## Abstract

**Background/Objectives:** Medical therapies that apply biodegradable materials, such as polydioxanone, are widely used to treat various disorders. Thread-embedding acupuncture (TEA) is a unique form of acupuncture that exerts long-lasting therapeutic effects by inserting absorbable threads at specific acupuncture points, and is widely used to treat various diseases. However, there is currently a lack of research regarding the safety of TEA. This prospective observational trial aims to evaluate the safety of TEA by collecting and analyzing data related to adverse events in patients receiving TEA in actual practice. **Methods:** A total of 350 eligible participants who undergo TEA at one of three university-affiliated hospitals and two traditional Korean medicine clinics will be systemically observed for post-treatment adverse reactions. The patients will be monitored at three time points: 1 week, 1 month, and 3 months post-treatment. Safety evaluations will assess the incidence of adverse events and treatment discontinuation rates during the 3-month post-treatment period. **Conclusions:** This study will evaluate the safety of TEA and provide information for decision-making in clinical practice as well as basic data for future large-scale research.

## 1. Introduction

Medical therapies that apply biodegradable materials, most commonly polydioxanone, are being utilized to treat various disorders and medical conditions. Thread-embedding acupuncture (TEA) is a type of acupuncture that involves the insertion of absorbable threads into the subcutaneous tissue or muscles for extended therapeutic stimulation. This specialized thread not only provides mechanical support, but also induces a localized inflammatory response, aiding in tissue recovery [1,2].

TEA has been practiced for centuries, supported by extensive clinical experience and empirical evidence in traditional East Asian medicine [3,4]. Unlike many conventional treatments that undergo preclinical evaluations before clinical application, TEA and similar practices in traditional East Asian medicine have followed a different pathway. These treatments have often been integrated into clinical practice first, based on long-standing empirical use and observed clinical benefits [5]. Subsequently, they undergo modern evaluations to systematically assess their safety and efficacy [6]. This approach reflects the practical, experience-based nature of East Asian medicine, where treatments are continuously refined through extensive real-world use.

TEA is used for various conditions, including musculoskeletal disorders [7,8], neurological conditions [9,10], allergic rhinitis [11], abdominal obesity [12], nonalcoholic fatty liver disease [13], and gastroesophageal reflux disease [14]. It is also applied in cosmetic procedures to reduce wrinkles and enhance skin elasticity [15,16]. Given its diverse applications, the materials and protocols used in TEA can vary significantly. Threads such as polydioxanone (PDO), polycaprolactone (PCL), and polylactic acid-glycolic acid are used, each with different degradation rates and tissue responses [17,18,19,20].

Despite its widespread use, there is a lack of systematic safety evaluations for TEA. Given that TEA is an invasive procedure, it carries the risk of adverse events (AEs), especially when performed by unskilled providers or in unsafe conditions [21]. Potential AEs include foreign body granuloma formation [22,23], skin infections [24], dimpling [25], and parotid gland injuries [26]. A retrospective study investigating the clinical effectiveness and safety of TEA in patients with facial palsy sequelae reported that more than 200 TEA treatments were administered in the 82 patients included in the study, with no serious adverse events (SAEs) or AEs requiring medical treatment [27]. In addition, a review article reporting AEs of TEA in musculoskeletal conditions found that 22 studies reported AEs out of a total of 97 retrieved articles, with 10 studies reporting no AEs or AEs unrelated to TEA. The most common AEs reported were redness, stiffness, and bruising, most of which were mild and transient [28]. However, retrospective studies have several limitations, such as those involving missing information, and selection and recall bias, due to the nature of the study’s design [29].

In a network meta-analysis of systematically evaluating the effectiveness and safety of acupuncture-related therapies in patients with polycystic ovary syndrome, 39 RCTs comparing 14 acupuncture-related therapies involving more than 4600 patients with polycystic ovary syndrome were analyzed. TEA and medication were the most frequently used treatments, followed by moxibustion and herbal medicine, moxibustion alone, acupuncture and medication, acupuncture–moxibustion and auricular acupuncture, and acupuncture and auricular acupuncture [30]. Nevertheless, existing clinical literature primarily consists of case reports and small-scale studies focusing on specific AEs [23,31]. Therefore, there is an urgent need for a well-designed prospective protocol to systematically assess the safety of TEA in real-world clinical settings.

This multicenter, prospective, observational study aims to address this gap by evaluating the safety of TEA. Previous studies have primarily focused on traditional acupuncture, which has been reported as safe in several large-scale sample surveys [32]. However, TEA, being a unique and more invasive form of acupuncture, requires a more comprehensive evaluation of its safety profile. This study aims to examine AEs associated with TEA and explore how patient-, practitioner-, and intervention-related factors influence these events, ultimately contributing to a better understanding of TEA’s safe practice.

## 2. Methods

### 2.1. Study Design, Setting and Aim

This multicenter, prospective, observational study will evaluate the safety of TEA in clinical practice. The study protocol is registered with the Clinical Research Information Service (CRIS; https://cris.nih.go.kr, (accessed on 16 December 2024); registration number KCT0008912). Participants will be recruited from three university-affiliated hospitals and two traditional Korean medicine clinics in Korea. Patients receiving at least one TEA treatment in a real-world setting, in line with the eligibility criteria, will be enrolled, and all AEs occurring in participants for a total of 3 months will be prospectively collected. In clinical practice, each patient will receive an appropriate number of TEA treatments based on their disease and condition; therefore, all additional TEA treatments after the first treatment will be collected as V2 to Vn in this study. Data regarding all TEAs received by participants and all AEs occurring during the study period will be collected and evaluated. The study procedure and assessment protocol for this trial are presented in Figure 1 and Table 1.

This study aimed to prospectively evaluate and validate the safety of TEA in real-world clinical practice. This observational approach enables the collection of safety data from a diverse patient population to reflect the complexities of actual clinical practice.

### 2.2. Participants

#### 2.2.1. Eligibility Criteria

Adults ≥ 19 years old who are scheduled to undergo TEA at one of the participating Korean medical institutions during the study period will be included in this study. Participants will be excluded if they have a condition or circumstance that the investigator determines may interfere with their participation in the study, such as having a serious comorbidity or inability to comply with the study protocol. In addition, each patient must provide written informed consent, demonstrate a clear understanding of the study’s objectives, comprehend the follow-up visit requirements, and express willingness to provide necessary information during follow-up visits.

#### 2.2.2. Recruitment Process

Patients undergoing TEA will be recruited from three university-affiliated hospitals and two traditional Korean medicine clinics in Korea. Recruitment will be carried out through direct referrals from medical staff at these institutions, as well as through consultation with the research team during routine clinical visits. No recruitment will be conducted using public advertisements. A total of 350 patients will be recruited (See the sample size calculation section below). Written informed consent will be obtained before initiating any research-related procedures. Patients will have the opportunity to ask questions regarding the study and will be assured that their decision to participate or not will not impact their clinical care.

### 2.3. Interventions

#### TEA Procedure

Standard TEA procedures will be followed, involving the insertion of absorbable threads using guide needles. For each participant, detailed information regarding the TEA procedure will be recorded, including the target disease or reason for undergoing TEA, such as cosmetic purposes, lumbar disorders, cervical disorders, shoulder disorders, elbow disorders, wrist disorders, knee disorders, ankle disorders, facial nerve palsy, facial spasm/twitch, temporomandibular joint disorders, gastrointestinal disorders, urinary system disorders, and gynecological disorders. The specific TEA products and their manufacturers will be documented. The types of threads used will include various compositions such as PDO and PCL, and forms, such as mono, multi, screw, and cog, based on the number of threads, twists, and the presence or absence of barbs [33]. The treatment areas will be carefully noted, covering the facial region, cervical region, shoulder region, lumbar region, gluteal region, thoracic and abdominal regions, upper limbs, and lower limbs. The number of thread insertions in each area will also be documented. Thread sizes, ranging from 7-0 to 3-0, and needle lengths and thicknesses will be recorded. The depth of thread insertion will be documented, with threads being inserted subcutaneously, into the fascia, intramuscularly, or into the periosteum. Concurrent treatments, such as acupuncture, moxibustion, and herbal medicine, will be permitted and recorded during the trial.

### 2.4. Data Collection

#### 2.4.1. Baseline Data

Demographic information, vital signs, medical history, concomitant medication and treatment details will be collected for each participant at the start of the study. This includes patient factors (age, sex, height, weight, blood pressure, pulse, body temperature, medical history, AEs of TEA within one year, medication history within one week, and concomitant medications or treatments), practitioner background factors (length of practice, affiliations, and board certification), and intervention factors (target disease, product manufacturer, thread material, thread shape, thread size, treatment area, number of needle insertions, needle length, needle thickness, and needling depth).

#### 2.4.2. AE Monitoring

Definition of AEs [34]: AEs are defined as any unfavorable or unintended signs, symptoms, or diseases temporally associated with the TEA procedure.

Monitoring Schedule: Patients will be monitored at baseline (V1: enrollment period and first TEA treatment), 1 week post-treatment (V1 + 7D), 1 month post-treatment (V1 + 1M), 3 months post-treatment (V1 + 3M), and during intermediate procedures performed within 3 months post-treatment (evaluated 1 week later—Vn + 7D). In addition, participants will be encouraged to self-report AEs at any time during the study period using an application or diary. Symptom confirmation and evaluation will be conducted on the designated assessment dates.

All symptoms will be independently assessed by an investigator blinded to the specific TEA details and subsequently confirmed for AEs by the practitioner who performed the TEA to ensure that no AEs are omitted that are unrecognized by the patient or the blinded assessor. Patients will also be encouraged to voluntarily upload photos of AEs to the self-reporting application if they would prefer, so that they can be independently assessed by blinded researchers and medical staff. In addition, depending on the AE, appropriate medical examination and management, including laboratory tests and imaging, will be applied until the AE resolves.

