#### 2.5.2. Statistical Methods

The analysis group will include participants who have received at least one TEA treatment. The main observation indicators, including the incidence rate of AEs and the treatment discontinuation rate, will be collected and analyzed without replacing the missing data. Continuous data will be represented using descriptive statistics, such as the number of participants, mean, and standard deviation, whereas categorical data will be presented as frequencies (N) or ratios (%). When necessary, a 95% confidence interval will be calculated. Unless otherwise specified, the statistical tests will be conducted using a two-sided significance level of 5%.

Student’s *t*-test will be used to compare normally distributed continuous variables and the Wilcoxon rank-sum test or Mann–Whitney U test will be used to compare non-parametric continuous variables between the patient groups with AEs and those without. A Shapiro–Wilk test and Kolmogorov–Smirnov test will be used to assess the normality of the distribution. The chi-square test (or Fisher’s exact test, when appropriate) will be used to compare dichotomous variables such as sex, the presence of comorbidities, and co-medications between the patient groups with and without AEs. Variables with *p* < 0.05 in the bivariate analysis or those considered clinically relevant will be included in the final regression model. The Kaplan–Meier method will be used to analyze the incidence of AEs and Cox proportional hazards regression will be used to analyze the differences in the incidence of AEs between subgroups including demographic characteristics, TEA materials or procedures.

All AEs collected in the study will be categorized according to the SOC and PT as defined in the MedDRA. The incidence and incidence rates will be presented by PT; however, multiple occurrences of the same AE by PT in the same subject will be considered as a single event. Furthermore, different discovered severities and causalities for the same AE will be treated as the maximum severities and causalities, respectively. Moreover, AEs associated with TEA and SAEs will be presented as events.

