### Strengths and Limitations

This study is the first to systematically evaluate the safety of TEA in real-world clinical settings across multiple centers.Detailed documentation of the TEA procedure, including regarding the target disease, TEA products and manufacturers, thread types and specifications, treatment areas, and insertion techniques, allows for a comprehensive analysis of potential risk factors.The observational study design enables the capture of both immediate and delayed AEs over a 3-month follow-up period.To minimize recall and reporting bias, a mobile application has been developed to enable patients to self-report AEs at their convenience, which will be independently assessed by blinded assessors and double-checked by the practitioner.As an observational study, it is not possible to definitively establish causality between TEA and AEs.This study is conducted in a single country, which limits its applicability in other countries; however, it includes a diverse range of healthcare organizations and patient populations to enhance the generalizability of the findings.Inherent observer bias may affect the interpretation of the results of this study, and we aimed to minimize this bias by implementing inter-rater standardization in this study.

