## Figures and Tables

**Figure 1 healthcare-13-00135-f001:**
[figure not shown]
Flowchart of the observational study. Abbreviations 7D, 1M, and 3M represent 7 days, 1 month, and 3 months after TEA treatment, respectively.

**Table 1 healthcare-13-00135-t001:** Schedule of observations. The ● indicates at which point of the trial the respective assessments will take place. Vn represents additional treatments administered within the 3-month observation period. In such cases, follow-up assessments are conducted 7 days after each additional treatment to monitor any adverse events. Continuous self-reporting means that during the 3-month follow-up period, patients are encouraged to report any adverse events at any time using an app or diary.

	Screening	Registration		Observation Period				
Time Point	Screening Visit (V0)	Baseline (V1)	Additional Treatments (Vn)	One Week Post-Treatment (V1+7D)	One Week Post-Additional Treatment (Vn+7D)	One Month Post-Treatment (V1+1M)	Three Months Post-Treatment (V1+3M)	Continuous Self-Reporting

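### Structured AE questioning thins to a 60-day gap after the first TEA and is added back only with further sessions, so late AE detection partly follows how often patients are asked

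*Protocol article*

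**What the plan says.** Section 2.4.2 of the protocol article fixes AE assessments after the first TEA (V1) at "1 week post-treatment (V1 + 7D), 1 month post-treatment (V1 + 1M), 3 months post-treatment (V1 + 3M), and during intermediate procedures performed" within the 3 months. The first three apply to every patient. The Table 1 legend adds that, where more treatments are given, "follow-up assessments are conducted 7 days after each additional treatment to monitor any adverse events". The body of Table 1 also marks the AE items at each additional treatment (Vn) itself. The number of sessions is not fixed: section 2.1 states that "each patient will receive an appropriate number of TEA treatments based on their disease and condition".

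Between these contacts, "participants will be encouraged to self-report AEs at any time during the study period using an application or diary" (section 2.4.2). Table 1 schedules self-reporting education at V1. Its continuous column covers occurrence, symptoms, onset and resolution dates, but not severity or causality. Self-reports are followed up at visits: "Symptom confirmation and evaluation will be conducted on the designated assessment dates".

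In section 2.5.2 the Kaplan–Meier method "will be used to analyze the incidence of AEs and Cox proportional hazards regression will be used to analyze the differences" between subgroups defined by demographics, thread material or technique. Among its strengths, the article says: "The observational study design enables the capture of both immediate and delayed AEs over a 3-month follow-up period".

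**The concern.** How often a patient is actively asked about AEs depends on two things: time since V1, and whether further TEA is given. A mild reaction that begins on day 40 and is gone by day 50 is found in a single-session patient only if the patient reports it unprompted or recalls it at 3 months. A patient still in treatment may be asked about it within days.

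Two stated uses of the data are exposed.

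- **Timing of AEs.** The Discussion expects AEs to be concentrated early. Sparse late questioning pushes the curve toward the same shape, so the study cannot cleanly test that expectation.
- **Risk factors.** Session number follows indication, and thread material, area and technique may follow indication too. A factor linked to repeated courses can show a higher AE hazard partly because its patients were asked more often.

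This is a matter of detection. It is separate from the real extra exposure that more sessions bring, and counting AEs per session would not remove it.

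**Working it through.** **The plan's own figure.** The article gives no figure for ascertainment. Its planning incidence is 12%, and its sample size reproduces: 0.12 × 0.88 × 1.96² / 0.035² = 331.2, and 331.2 / 0.95 = 348.6, so 349. The 12% serves as the true incidence in step 4.

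**1. Gaps between structured assessments.** With 1 month = 30 days and 3 months = 90 days (assumed), the gaps are 7, 30 − 7 = 23 and 90 − 30 = 60 days. With 28-day months they are 7, 21 and 56; with calendar months about 7, 24 and 61.

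**2. Schedules compared.** Session patterns are assumed; the rules come from section 2.4.2 and Table 1.

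| Sessions | Assessment days after V1 | Number | Largest gap (days) |
|---|---|---|---|
| One | 7, 30, 90 | 3 | 60 |
| Four weekly | 7, 14, 21, 28, 30, 90 | 6 | 60 |
| Eight weekly | 7, 14, 21, 28, 30, 35, 42, 49, 56, 90 | 10 | 34 |
| Six, 14 days apart | 7, 14, 21, 28, 30, then weekly 35 to 77, 90 | 13 | 13 |

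**3. Detection of AEs starting in days 30–90.** Assume a constant hazard and brief AEs, with the chance of recalling an unreported AE halving every h days. Averaged over a gap of length L, detection is h / (L ln 2) × (1 − 0.5^(L/h)). Take h = 14, so h / ln 2 = 20.2.

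- One session (one gap of 60): 20.2 × (1 − 0.051) / 60 = 0.319.
- Eight weekly (gaps 5, 7, 7, 7, 34): 20.2 × (0.219 + 3 × 0.293 + 0.814) / 60 = 0.644. Ratio 0.644 / 0.319 = 2.0.
- Four weekly: again one gap of 60, so 0.319 and ratio 1.0.
- Three monthly sessions (gaps 7, 23, 7, 23): 20.2 × (2 × 0.293 + 2 × 0.680) / 60 = 0.655. Ratio about 2.0 to 2.1.

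For eight weekly sessions against one, h = 7 gives 0.481 / 0.168 = 2.9 and h = 60 gives 0.886 / 0.721 = 1.2.

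Within a single-session patient, week-1 detection at h = 14 is 0.845. A constant hazard would then appear to fall 0.845 / 0.319 = 2.6-fold by days 30–90, again with no self-reporting.

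Now let a share q of AEs be self-reported, so detection is q + (1 − q)d:

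| q | One session | Eight weekly | Ratio |
|---|---|---|---|
| 0 | 0.319 | 0.644 | 2.0 |
| 0.5 | 0.660 | 0.822 | 1.25 |
| 0.8 | 0.864 | 0.929 | 1.08 |

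**4. Overall 3-month incidence.** A simulation gave both groups the same true 12%. It assumed 80% of AEs within 14 days, mean AE duration 7 days, and recall of a resolved AE decaying with a mean of 7 to 30 days. It compared six sessions 14 days apart with one.

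| Self-reporting | Ratio, all AEs | Ratio, onset after day 14 |
|---|---|---|
| 0 | 1.14–1.30 | 1.60–2.66 |
| 30% | 1.09–1.18 | 1.35–1.72 |
| 60% | 1.05–1.09 | 1.17–1.30 |
| 90% | 1.01–1.02 | 1.04–1.06 |

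At the unfavourable end, detected incidence is 8.0% (one session) against 10.4% (six); at the favourable end, 11.8% against 12.0%. At 30% self-reporting and 14-day recall, the overall ratio is 1.09 if 95% of AEs are early and 1.27 if 50% are.

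**The case against.** The strongest reply is that the protocol already has a safeguard. Every patient is taught to self-report at V1, and the app is offered expressly against recall and reporting bias. The practitioner also reviews each patient for AEs that the patient or the blinded assessor missed. An AE still present at 3 months can be seen there. This stands, and it means the 60 days are a gap between structured assessments, not a period without capture. But self-reporting is only encouraged, and neither a visit examination nor practitioner review recovers a short-lived AE that resolved unreported.

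Second, the pilot places most AEs within 14 days, most often on the procedure day, and every patient has the same day-7 check. This stands too: it limits the effect on overall incidence. It does not protect the claim to capture delayed AEs.

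Third, eight weekly sessions has no basis in the documents. The one sessions-per-patient figure, in the Introduction, is over 200 treatments in 82 patients, about 2.4 each. Four weekly sessions give no late difference at all. So questioning does not become dense again in every multi-session patient; spacing decides, as the three-monthly case shows.

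A reader might also infer that the analysis wrongly omits adjustment for assessment frequency. The documents do not support that. An analysis plan may exist, and section 2.5.2 already admits clinically relevant variables to the model. The point rests on the assessment schedule, which the protocol itself fixes.

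**Conclusion.** The point holds as a weakness of data collection, worth correcting because the correction is cheap. Detection of later, short-lived, unreported AEs depends on time since V1 and on session number, and no later analysis recovers AEs that were never elicited.

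The size cannot be derived from the documents; session patterns, recall decay and self-report rates are all assumptions. The late-period ratio of 2.0 is an upper-end illustration with no self-reporting and a constant hazard, and must not be read as the expected bias in the 3-month Cox contrasts. Across the assumptions tried, the overall distortion runs from about 1.01 to 1.3.

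Two stronger readings are tempting. One is that late flattening of the curve will be an artefact. The pilot expects flattening anyway, and the documents cannot separate the two causes. The other is that a higher AE rate in multi-session patients would be spurious. Extra assessments coincide with extra TEA exposure, so such a difference would mix real risk with added detection.

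**What to change.** **Data collection.** In section 2.4.2 and Table 1, add a fixed weekly prompt through the existing app or diary for every patient from V1 to V1+3M, whether or not further TEA is given: any new symptom since the last prompt, yes or no, with onset date. For patients who answer, no gap then exceeds 7 days, and under the step 3 assumptions (h = 14) detection is about 0.85 in every week. The cost is about 13 short prompts per patient (90 / 7 = 12.9) and slight patient burden.

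**Patients already followed without prompts.**
- Keep the planned 3-month analyses.
- Add a sensitivity analysis of the factor comparisons limited to AEs with onset within 7 days after a session, accounting for the number of sessions. Every session is followed by a 7-day check, so this window is common to all. It should not replace the main analysis: it drops delayed AEs, which are a stated aim, and the pilot's early window is 14 days, not 7.
- Report AEs with later onset by interval (day 8 to 1 month, 1 to 3 months) as a lower bound.
- Do not take late flattening of the Kaplan–Meier curve alone as evidence that delayed AEs are rare.

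These additions cost a few sentences in section 2.5.2, and the sensitivity analysis will have fewer events than the main one.

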By enrolling a large and diverse patient population across multiple centers, we aim to capture a comprehensive range of AEs and their potential correlations with different treatment parameters. Detailed documentation of each TEA procedure, including the type of threads, insertion techniques, and treatment areas, allows for a thorough analysis of factors that might influence the occurrence of AEs. Additionally, this study aims to evaluate safety with follow-up periods extending up to 3 months post-treatment. In our preliminary pilot study, most AEs occurred within the first 14 days, most often on the day of the procedure, and resolved spontaneously without any medical treatment. Furthermore, no additional AEs were observed after 3 months, suggesting that AEs were concentrated early on [45]. In addition, previous systematic reviews have reported that AEs following TEA were predominantly local reactions, most of which were mild, transient, and occurred in the acute post-treatment period [28,38]. This approach allows for the capture of both immediate and delayed AEs, contributing to a more comprehensive safety profile of TEA. Our systematic approach to data collection and analysis aims to contribute to improving evaluations in traditional East Asian medical practices. The systematic recording of treatment details and AEs can be applied to acupuncture, moxibustion, and herbal medicine studies.

For practitioners, understanding the risk profiles associated with different TEA techniques and materials can guide safer practice and improve patient outcomes. For patients, transparent safety information can help with making informed decisions regarding their treatment options. For researchers, the data will provide a foundation for further investigations into the mechanisms underlying AEs and the development of strategies to mitigate risks. Additionally, regulatory bodies and policymakers can use the findings to establish guidelines and standards for the safe practice of TEA and similar other interventions.

In conclusion, this study aims to contribute to the body of knowledge regarding the safety of TEA by providing systematic and comprehensive safety data. The data generated in this trial will serve as a foundation for further investigation and the development of evidence-based clinical guidelines.

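### Severity is not collected when a patient self-reports an AE, so short AEs starting after day 7 will often have resolved before they are first graded

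*Protocol article*

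**What the plan says.** Section 2.4.2 sets up two channels. The first is scheduled: a patient with a single session is assessed 1 week, 1 month and 3 months after it. For patients treated again, the legend of Table 1 adds that "follow-up assessments are conducted 7 days after each additional treatment to monitor any adverse events". The second is continuous: "participants will be encouraged to self-report AEs at any time during the study period using an application or diary". The next sentence of 2.4.2 joins the two: "Symptom confirmation and evaluation will be conducted on the designated assessment dates".

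The Safety Assessment block of Table 1 follows the same division. The continuous self-reporting column is marked for incidence, symptoms, date of onset and date of resolution. It is blank for severity and causality, which are marked only at Vn, V1+7D, Vn+7D, V1+1M and V1+3M.

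Section 2.4.3 makes severity one component of the outcome. Section 2.5.2 says that when the same AE carries different severities, the maximum is analysed. On the natural course, the Discussion reports from the pilot that "most AEs occurred within the first 14 days, most often on the day of the procedure, and resolved spontaneously without any medical treatment". Under Strengths and Limitations the app is presented as the safeguard: "To minimize recall and reporting bias, a mobile application has been developed".

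**The concern.** Text and table agree, so this is a design choice and not a contradiction. The difficulty is that the app records that an AE happened, what it was and when it began and ended, but not how bad it was. For a single-session patient there is no grading point between day 7 and 1 month, and none between 1 month and 3 months. The document itself expects AEs to be mostly early and to resolve spontaneously. A brief AE starting after day 7 can therefore begin and end between two grading points.

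The assessor then grades a symptom that is no longer present, and the analysis needs its peak, because section 2.5.2 takes the maximum severity. Peak severity that was not recorded at the time cannot be recovered later. The recall problem that the app is meant to reduce remains for this component of the outcome. Closeness of grading to the event also depends on the course of treatment, since patients with further sessions are seen at Vn and Vn+7D as well.

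**Working it through.** **Inputs.** Grading dates for one session are V1+7D, V1+1M and V1+3M (2.4.2, Table 1). *Assumption:* 1 month is day 30 and 3 months is day 90. The gaps are 30 − 7 = 23 days and 90 − 30 = 60 days. The document gives no AE durations and no share of AEs starting after day 7, so both are varied below.

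**Step 1: wait from onset to first grading** (next designated day minus onset day).

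- Onset day 8: 30 − 8 = 22 days
- Onset day 14: 30 − 14 = 16 days
- Onset day 31: 90 − 31 = 59 days

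Any AE starting on days 8 to 14 and lasting less than 16 days is over before it is graded.

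**Step 2: share of AEs starting after day 7 that resolve before the next grading date**, for a fixed duration of D days.

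- Onset uniform over days 7–90: [max(0, 23 − D) + max(0, 60 − D)] / 83
- Onset uniform over days 7–14: (23 − D) / 7, limited to 0–1
- Onset uniform over days 7–30: max(0, 23 − D) / 23

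| D (days) | Days 7–90 | Days 7–14 | Days 7–30 |
|---|---|---|---|
| 3 | 77/83 = 93% | 100% | 20/23 = 87% |
| 7 | 69/83 = 83% | 100% | 16/23 = 70% |
| 10 | 63/83 = 76% | 100% | 13/23 = 57% |
| 14 | 55/83 = 66% | 100% | 9/23 = 39% |
| 20 | 43/83 = 52% | 3/7 = 43% | 3/23 = 13% |
| 28 | 32/83 = 39% | 0% | 0% |

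The share passes one half at D = 20.75, 19.5 and 11.5 days respectively.

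With exponential durations of mean m and onset uniform over days 7–90, the share is [23 − m(1 − e^(−23/m)) + 60 − m(1 − e^(−60/m))] / 83. This gives 83% for m = 7, 70% for m = 14 and 51% for m = 28.

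**Step 3: effect of further sessions.** As an illustration, assume extra sessions on days 14 and 28. Grading dates become 7, 14, 21, 28, 30, 35 and 90. For D = 7 and onset uniform over days 7–90, only the 35-to-90 gap exceeds D, so the share is (55 − 7)/83 = 58%. For D = 14 it is (55 − 14)/83 = 49%.

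**Step 4: how many patients.** The only AE rate in the design is the 12% of section 2.5.1. That calculation reproduces: 0.12 × 0.88 × 1.96² / 0.035² = 331.2, and 331.2 / 0.95 = 348.6, rounded up to 349. At 12%, 0.12 × 350 = 42 patients would have an AE. If 5% to 30% of these began after day 7 (assumed range), that is 2.1 to 12.6, or about 2 to 13 patients.

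**Step 5: what the other provisions can supply.** Photos can be sent, but only if patients "voluntarily upload photos of AEs to the self-reporting application if they would prefer, so that they can be independently assessed by blinded researchers". Among the symptoms in Table 2, pain, paresthesia, pruritus and fatigue do not show in a photo. Examination between visits is possible, since "depending on the AE, appropriate medical examination and management, including laboratory tests and imaging, will be applied until the AE resolves", but it depends on the AE and is not described as severity grading. No time limit is given for assessing an app report or a photo.

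**The case against.** The strongest reply is that the grader does not start from nothing. Symptoms, onset and resolution can be logged as they happen, photos can go to blinded staff, and some AEs will be examined before the next visit. AEs in the pilot arose most often on the procedure day, and those reach a graded visit within 7 days. The single-session patient is the worst case, and nothing shows how common that patient is. All of this stands, and it limits the point. None of it supplies a severity rating made at the time for an AE with no photo and no interim examination.

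A reader might infer three stronger things that the document does not support.

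- **Most later AEs are graded from recall.** The document gives no durations, and step 2 shows that the majority depends on them. Recall is also only one source, beside dated app or diary entries and optional photos.
- **Causality ratings are compromised in the same way.** The factors listed in 2.4.3 include timing, recurrence on repeat treatment, alternative causes and improvement after stopping. Timing is self-reported as it happens, and several of the others can only be judged later.
- **Every self-report needs prompt assessor contact, with the rating nearest the event used in the analysis.** Contact would be triggered by each report, not by each of the patients expected to have an AE, so it costs much more than a field. A nearest-rating rule would also conflict with the maximum rule in 2.5.2.

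**Conclusion.** The point holds for severity only. For a single-session patient, a short AE starting after day 7 will often have resolved before it is first graded, with waits of 22, 16 and 59 days for onset on days 8, 14 and 31. These waits rest on taking months as 30 days; the word often rests on AEs lasting no more than about 10 days, for which over half resolve first under every onset pattern tried. For longer AEs the answer depends on when they start.

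The number of patients affected cannot be derived from the document. About 2 to 13 of 350 is an illustration under an assumed late share, and the group is probably a minority of those with AEs. The count of self-reported AEs, and with it the overall incidence estimate, is not affected. This is a cheap improvement to a stated outcome and does not invalidate the study.

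**What to change.** In section 2.4.2 and Table 1, mark severity under continuous self-reporting by adding a patient-rated severity item to the existing app and diary entry, completed at onset and at worst. State that the blinded assessor uses this contemporaneous rating when grading the AE at the next designated visit. Keep the maximum-severity rule of section 2.5.2; the rating at worst gives the assessor the information that this rule calls for. Leave causality at the designated visits.

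The cost is one more field per report and slightly more patient burden. No extra visits or calls are needed, and the sample size does not change. AEs from the first week, which can wait up to 7 days for a grade, benefit from the same field.
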